## **2.2. Detailed research plan**

### **2.2.1. Overall hypothesis and general aims**

The overall aim of this multicenter, cluster randomized-controlled trial is to investigate whether checklist-guided shared decision-making including decision aids and communication of expected outcome influences patients' decision regarding DNR code status, and at the same time improves decision-making quality as judged by patient decisional comfort, patient knowledge, and involvement in decision-making and patient satisfaction. As recommended for interventional trials, the study protocol was published at [clinicaltrials.gov](https://clinicaltrials.gov/ct2/show/NCT03872154) (<https://clinicaltrials.gov/ct2/show/NCT03872154>).

### **2.2.2. Setting and collaboration**

This multicenter study will be conducted in six participating Swiss teaching hospitals, namely the University Hospital Basel, the Kantonsspital Aarau, the University Hospital Bern (Inselspital), the Cantonal Hospital Baselland Liestal, the St. Claraspital Basel and the Cantonal Hospital Lucerne. The head of departments at the different locations have agreed to give full support for this study. The local investigators will support the study with personal resources and by including patients. Our main study team from the University Hospital Basel will be responsible for the study set-up, recruitment and training of the study nurses, who support data collection and data cleaning as part of the ancillary project.

### **2.2.3. Patient population, inclusion, and exclusion criteria**

Residents on the medical wards will be the primary level of randomization. We have no exclusion criteria for physicians except if they refuse participation. Outcomes will be assessed in patients treated by these physicians. Any adult (>18 years) patient that is admitted for in-hospital care will be eligible. There will be no exclusion based on the type of illness, comorbidity or severity of illness in order to include a representative population of patients in Swiss hospitals. We will exclude patients unable to complete questionnaires or unable to follow code status discussions due to (1) intoxication, (2) paracsis; (3) serious psychiatric conditions (e.g., psychosis, depression with suicidal tendency, stupor), (4) cognitive impairment (e.g. dementia, delirium). Also, patients prior included in this study (i.e., patients who are hospitalized for the second time) are not eligible. Patients, in whom resuscitation attempts would be futile, will not be included in this study.

Recently Ebell et al developed the GO-FAR score, a clinical risk score to predict the estimated likelihood of neurologically intact survival of patients after in-hospital resuscitation[41]. The authors developed a multivariate prediction model based on 51`240 patients who experienced in-hospital cardiac arrest and calculated cut-off scores indicating likelihood of functional survival. The two lowest categories represent very low (<1%) and low (1-3%) likelihood of survival. It has therefore been suggested that these patients should be considered futile regarding CPR attempts [42]. Another tool to assess whether patients are at increased risk for poor outcome is the Clinical Frailty Scale[43]. This 9-category scale combines cognitive and physical aspects of frailty such as comorbidity, cognitive impairment, and disability. Research has shown that the scale, which is increasingly used in routine screening of older patients, predicts short-term mortality[44, 45]. However, the prevalence of futility in hospitalized patients upon admission assessed through the GO-FAR score and the Clinical Frailty Scale has not been systematically investigated.

According to the literature, we will define futility as a GO-FAR score  $\geq 14$  or patients in categories 7-9 in the Clinical frailty scale.

#### **2.2.4. Informed consent statement**

The study was approved by the local Ethics Committee (Ethics Committee northwest/central Switzerland; Ethikkommission Nordwest- und Zentralschweiz; EKNZ as well as the Ethics Committee Bern). All residents responsible for in-hospital admissions in the participating study centers will be asked to participate in our study and to provide written informed consent. For the main endpoint of the study (code status), the Ethics Committees agreed, that patient level informed consent is not necessary, due to the cluster randomization design. However, all patients will be asked to give written informed consent for completion of questionnaires related to secondary endpoints.

#### **2.2.5. Study flow**

Code status discussions are usually conducted by the treating residents on the ward. Residents that agree to participate will be randomized into the intervention or control group with a 1:1 allocation (see Figure 1). Randomization will be done by a pre-specified, computer-generated, web-based randomization scheme (block randomization with variables sizes of 4 to 6). The randomization will be stratified for the trial site. The CTU Basel is responsible for the integrity of the randomization procedures and randomization will be electronically integrated in the SecuTrial® website, where also all data collection for this trial is done.

The study will be conducted for admissions from Monday to Friday. Admission on medical wards normally takes place between 8:00 am and 4:00 pm. Residents that participate in our study will report all new admissions to our study team. Additionally, we will check the hospital's database and the hospital's bed managers will provide us with a list of planned hospitalizations one day in advance. A member of our study team will then check whether the new patient is eligible for trial inclusion.

#### **Figure 1. Study flow**

[figure not shown]

Baseline data will be entered into a centralized web-based study software (SecuTrial®) provided by the Clinical Trial Unit (CTU). The following baseline-data will be recorded for each patient:

- Socio-demographics (e.g., age, gender, socio-economic status, religion,)
- Health-related quality of life defined by EQ-5D (EuroQol)[46]
- Medical situation (i.e., complete list of main diagnosis and comorbidities)

To enable blinding of patients and physicians regarding the intervention and main endpoint of our trial, we will not share any detailed information, but ask for their participation in a trial comparing two different communication strategies on the quality of code status discussions. Yet, blinding of the study coordinator is not feasible. After code status discussion, a member of our research team will interview patients and residents separately. Using a structured questionnaire, patient outcomes and perceived quality of care as defined below (2.2.8. primary and secondary endpoints) will be assessed. In addition, the physician's perception of the code status discussion will be examined using a structured questionnaire.

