There are several challenges to the current practice of code status discussions. First, these discussions are complex as objective medical facts and personal perspectives of physicians and patients both need to be integrated in the communication. Second, several studies found code status discussions to be ineffective due to poor communication skills of physicians[14, 15], which is particularly true for inexperienced residents[16]. Code status discussions are often conducted in a non-personalized way, missing the chance to focus on patients' values and goals[17]. Insufficient time during patient encounters pose an additional barrier for optimal communication[18-20]. Furthermore, the decision-making during code status discussions is often challenged by uncertainty around interventions and therapies that might be available, but whose outcomes remain uncertain[21, 22].

Importantly, patients with in-hospital cardiac arrests have a poor prognosis with a survival to hospital discharge rate of less than 20%[23, 24]. Furthermore, 40% of survivors suffer from substantial neurologic

deficits limiting their possibility to live an independent life[25]. In 2012, a British multi-center cohort study investigated medical charts of patients that had undergone resuscitation of an in-hospital cardiac arrest[26]. In more than 75% of patients that received CPR, the code status was unknown and 67% of patients that were resuscitated, actually had an underlying pre-existing fatal disease. Importantly, an independent assessment of all cases found that a DNR status would have been appropriate in 85% of cases, because the risk / benefit ratio was unfavourable for the patient, indicating medical futility. In addition, a recent cancer study shows that physicians often rather document a presumed code status, than conduct a discussion, leading to a high proportion of full code status despite severe illnesses of a patient [27]. Almost a third of patients that were presumably documented as full code would have preferred DNR code status[27].

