## *Study protocol and statistical analysis plan*

We will use cluster specific methods because residents rather than patients are randomized, and we expected that variance in how patients are managed would be partly explained by the resident. We will further account for the level of the participating center (hospital), as DNR discussions may vary according to study center. For each of the outcome measures we will test the null hypothesis that the likelihood of the outcome is the same in both study groups after accounting for some baseline characteristics (i.e., age, gender, main medical diagnosis). We will use hierarchical logistic regression to test for an effect of the intervention on any binary outcome measures and linear regression for any continuous outcome measure.

All analyses will be conducted using Stata. All analyses were performed using STATA 15.1 (Stata Corp, College Station, TX). For all analyses, we accept a type I error rate of  $\alpha = 5\%$ .

The design of our study and statistical approach was developed in close collaboration with statisticians and epidemiologists of the Clinical Trial Unit (CTU) of the University Hospital Basel.

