### **2.3.10 Power and sample size considerations**

For sample size calculation, we consider the intra-cluster correlation coefficient, the number of events, the expected effect, and the power of the study. Based on pilot data in this patient population, we expect that 30% of patients in the usual care control will have a DNR code status, which will increase to 45% in the intervention group. We plan to include 174 residents (cluster) with a mean of 5 eligible patients per week over a 3-week period (total of 15 patients per cluster) in the five participating centers over a total study time of 2 years. Based on these assumptions, we will include 2610 patients among 174 residents, which will give this study an 80% power at a 0.05 alpha error with an inter-cluster correlation of 0.5. Because the inter-cluster correlation in this setting is unknown, we used a conservative estimate above, but plan to possibly adjust the sample size based on a blinded interim analysis after data of 30 residents (cluster) is collected. In this interim analysis, we estimate the intraclass correlation of code status decisions, i.e., how much the code status decisions are cluster-dependent. Based on this estimation of intraclass correlation, we will adjust the total required sample size.

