However, informing a patient that resuscitation measures in case of a cardiac arrest are judged as futile and setting a DNR status is complex and challenging. Due to their limited experience in code status discussion, this might be especially true for unexperienced medical residents.

In this ancillary project we aim to examine, whether a communication workshop and a checklist for communication about futility is associated with a higher rate of DNR code status in patients who are considered futile according to either the Go-Far Score or the Clinical Frailty Scale.

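### Apart from hospital, the plan lists no baseline variable for the randomised unit; recording residents' year of training and adjusting for it would be a cheap improvement of unknown gain.

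*Combined protocol and SAP*

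**What the plan says.** Residents are allocated 1:1 (Section 2.2.5). On balance: "The randomization will be stratified for the trial site". No other stratification factor is named.

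Baseline data are introduced in Section 2.2.5, after Figure 1, with "The following baseline-data will be recorded for each patient". The items are patient socio-demographics, EQ-5D and diagnoses with comorbidities. Physician data (Sections 2.2.5 and 2.2.8) are perceptions of the discussion and the surprise question. The physician's perception is asked for after the discussion, so it cannot serve as a baseline covariate.

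Section 2.3.9 tests each outcome "after accounting for some baseline characteristics (i.e., age, gender, main medical diagnosis"). It uses cluster-specific methods for residents and accounts for hospital.

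Section 2.1 attributes ineffective code status discussions to poor communication skills, "which is particularly true for inexperienced residents[16"]. Section 2.4, on the parallel futility study, says of the difficulty of those conversations that "this might be especially true for unexperienced medical residents".

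Section 2.3.10 sizes the trial on 174 residents ("total of 15 patients per cluster"), "which will give this study an 80% power at a 0.05 alpha error with an inter-cluster correlation of 0.5". It describes that correlation as unknown and the value as conservative, and plans to revise the sample size after a blinded look at 30 residents.

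**The concern.** In a cluster-randomised trial, a covariate helps most when it explains variation between the randomised units. At the planning ICC nearly all the noise in the primary comparison sits there. The named covariates are patient-level and act mainly on the small remainder, although they may absorb some between-resident variance where residents' case mix differs.

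Experience is the obvious candidate at resident level. The intervention is communication training, and the protocol itself ties inexperience to poorer discussions. Several secondary endpoints measure the quality of the discussion directly: decisional conflict, involvement, satisfaction and physician confidence.

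Two things are at stake. One is possible extra power at almost no cost. The other is being able to describe the randomised units by arm beyond their hospital, and so to see a chance imbalance in seniority. Stratifying by site does not balance seniority within a site. Both matter more if the interim step reduces the number of residents.

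**Working it through.** **Inputs.** Section 2.3.10: "30% of patients in the usual care control will have a DNR code status, which will increase to 45" per cent; alpha 0.05, taken as two-sided because that reproduces the plan; power 80%; ICC 0.5; m = 15 patients per resident; 174 residents. R2, the share of between-resident variance explained by resident variables, is not in the documents. It is an assumption, varied from near 0 to 30%.

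**1. Reproduce the plan.** Two proportions, pooled variance, no continuity correction:

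n = [1.96 × √(2 × 0.375 × 0.625) + 0.842 × √(0.30 × 0.70 + 0.45 × 0.55)]² / 0.15² = 162.3, so 163 per arm.

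Design effect = 1 + (15 − 1) × 0.5 = 8. Total = 2 × 163 × 8 = 2608 patients. Divided by 15 this is 173.9, so 174 residents and 2610 patients. The plan's figure reproduces. Power with 87 residents per arm is 80.2%.

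**2. Where the variance lies.** The variance of a resident's DNR proportion is proportional to ICC + (1 − ICC)/m = 0.5 + 0.5/15 = 0.533. The between-resident share is 0.5/0.533 = 93.8%. At ICC 0.2 it is 78.9%, and at ICC 0.1 it is 62.5%. This share includes any differences between hospitals, which the plan already addresses.

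**3. Effect of a resident-level covariate.** Design effect = (1 − ICC) + m × ICC × (1 − R2). At ICC 0.5 with 174 residents:

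| R2 (assumed) | Design effect | Variance reduction | Power |
|---|---|---|---|
| 0 | 8.00 | 0% | 80.2% |
| 2% | 7.85 | 2% | 80.9% |
| 5% | 7.63 | 5% | 82.1% |
| 10% | 7.25 | 9% | 83.9% |
| 20% | 6.50 | 19% | 87.7% |
| 30% | 5.75 | 28% | 91.3% |

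**4. If the true ICC is lower and 174 residents are kept.** Unadjusted power is already 98.3% at ICC 0.2 and 99.9% at ICC 0.1. The power gain is then negligible.

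**5. If the interim step cuts the number of residents to match.**
- ICC 0.2: design effect 3.8; 163 × 3.8/15 = 41.3, so 42 per arm and 84 residents. Power is 80.8% unadjusted, and 83.9% to 90.1% with R2 of 10% to 30%.
- ICC 0.1: design effect 2.4; 163 × 2.4/15 = 26.1, so 27 per arm and 54 residents. Power is 81.5% unadjusted, and 83.9% to 88.7% with R2 of 10% to 30%.

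**6. Chance imbalance.** Assume that half of the residents are junior. The difference in junior share between arms has standard error √(2 × 0.25/k), with k residents per arm. By the normal approximation:

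| Residents | Arms differ by more than 10 points | By more than 20 points |
|---|---|---|
| 174 | 19% | 1% |
| 84 | 36% | 7% |
| 54 | 46% | 14% |

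**The case against.** The case against is that this is a preference and that nothing is broken. Much of it stands.

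- **The trial is not underpowered for want of this covariate.** A reader might infer that it is. The 80% is reached with no adjustment. A chance imbalance in seniority neither biases the estimator nor invalidates the test, because the resident-level analysis carries that uncertainty.
- **The plan does not claim that half the variation in DNR lies between residents.** Section 2.3.10 calls the ICC unknown and 0.5 conservative, so the 94% is a property of a cautious planning value.
- **Experience is not named as a driver of DNR choice.** Section 2.1 links it to communication skills, and Section 2.4 to the difficulty of futility conversations in a different population. Neither says that DNR rates differ by seniority. R2 for the primary endpoint could be near zero.
- **Resident-level factors are not ignored altogether.** Hospital is stratified on and accounted for.
- **The formula is approximate.** It works on the scale of cluster proportions, whereas the primary model is hierarchical logistic. There, adjustment shifts the conditional odds ratio and need not shrink its standard error; the benefit appears mainly as power.
- **Secondary endpoints cannot be quantified.** No ICC is given for any of them.
- **The baseline list is a list of patient data.** Its silence on residents does not prove that nothing is collected. It shows only that nothing is specified.

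The argument that a low true ICC makes adjustment pointless holds only if 174 residents are kept. Section 2.3.10 provides for resizing to the estimated ICC. If the number is cut to match, the surplus power goes, and step 5 shows a possible gain again.

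**Conclusion.** The point stands as a low-cost improvement, not as an error. Apart from hospital, the plan specifies no baseline variable for the unit it randomises, although its own background section singles out inexperience as a problem in these discussions.

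At the planning ICC, the possible gain runs from nothing to about 11 percentage points of power (80.2% to 91.3%) over an assumed R2 of 0 to 30%. If the ICC proves low and the number of residents is cut accordingly, the gain is about 2 to 9 points for R2 of 10% to 30%. If the ICC proves low and the number is kept, there is little to gain in power.

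These figures rest on the linear-scale approximation, 15 patients per resident, and an R2 that the documents do not supply. What does not depend on R2 is that the randomised units could be described, and an imbalance in seniority seen.

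**What to change.** At resident consent, before randomisation, record year of training and previous communication or shared-decision training; months on medical wards could be added. Residents already give written consent (Section 2.2.4), and randomisation and data collection share one electronic system (Section 2.2.5). Answers given before allocation cannot be influenced by it.

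In Section 2.3.9, pre-specify year of training as a resident-level covariate in the models for DNR status and for the Decisional Conflict Scale, beside hospital and the patient covariates. Report the resident variables by arm in the baseline table. Because R2 is unknown, do not build an expected gain into the sample size.

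Cost: two or three questions per resident, one model term and about one degree of freedom. No extra visits or staff are needed.

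### Baseline EQ-5D is recorded but left out of the adjustment set, so the patient-reported outcomes may carry some health-status imbalance and lose a little precision

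*Combined protocol and SAP*

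**What the plan says.** Section 2.2.5 (Study flow, baseline data below Figure 1) lists three groups of data recorded for each patient: socio-demographics, "Health-related quality of life defined by EQ-5D (EuroQol"), and the main diagnosis with comorbidities. It does not say whether EQ-5D is completed before or after the code status discussion.

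Section 2.3.9 says that each outcome is compared between arms "after accounting for some baseline characteristics (i.e., age, gender, main medical diagnosis"). The list is introduced by i.e., so it reads as closed. Continuous outcomes are analysed by "linear regression for any continuous outcome measure". Resident-level clustering is to be handled, and on centre the plan adds: "We will further account for the level of the participating center (hospital), as DNR discussions may vary according to study center".

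On the order of events, section 2.2.5 says: "Residents that agree to participate will be randomized into the intervention or control group with a 1:1 allocation". After that, "Residents that participate in our study will report all new admissions to our study team", with a cross-check against the hospital database and the bed managers' lists, and "A member of our study team will then check whether the new patient is eligible for trial inclusion". On blinding it adds: "Yet, blinding of the study coordinator is not feasible". Under section 2.2.4, patients consent individually to the questionnaires for secondary endpoints, whereas code status needs no patient consent.

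**The concern.** EQ-5D is the only patient-rated health measure listed at baseline. It could plausibly be related to decisional conflict, fear, disturbance and satisfaction, although the documents give no correlation. The plan collects it and then does not use it in the comparison.

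The design gives a particular reason to care. Randomising residents balances residents. Patient-level balance also depends on who is identified, found eligible and willing to answer questionnaires, and all of that happens after the resident's allocation. Age, gender and main diagnosis describe health status only in part. If the questionnaire respondents in one arm are in somewhat worse health, the estimate for the key secondary endpoint shifts, and recruiting more residents would not remove a systematic shift. A smaller matter is precision: patient-level variance that a measured baseline score could explain stays in the error term.

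**Working it through.** **The plan's own figure.** Inputs from section 2.3.10: 30% against 45%, 80% power, alpha 0.05 (taken as two-sided), ICC 0.5, 15 patients per resident.

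- Two-proportion formula without continuity correction: 163 patients per arm.
- Design effect: 1 + (15 - 1) x 0.5 = 8, so 163 x 8 = 1304 per arm.
- 1304 / 15 = 86.9, rounded up to 87 residents per arm. That gives 174 residents and 174 x 15 = 2610 patients.

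The stated total reproduces. It concerns the primary endpoint and does not depend on EQ-5D. The layout of 87 residents per arm with 15 patients each is used below, assuming that all patients answer.

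**Precision.** The documents give no SD, ICC or EQ-5D correlation for any patient-reported outcome. Assumed: ICC of 0.05 or 0.5 (the latter is the plan's value for code status), and EQ-5D explaining a share R2 of 5-15% of within-resident variance beyond age, gender and diagnosis. With the outcome SD set to 1:

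Variance of a resident's mean = ICC + (1 - ICC)(1 - R2)/15

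| ICC | Variance without EQ-5D | R2 | Fall in variance | Fall in SE |
|---|---|---|---|---|
| 0.05 | 0.05 + 0.95/15 = 0.1133 | 0.05 | 2.8% | 1.4% |
| 0.05 | 0.1133 | 0.10 | 5.6% | 2.8% |
| 0.05 | 0.1133 | 0.15 | 8.4% | 4.3% |
| 0.5 | 0.5 + 0.5/15 = 0.5333 | 0.05 | 0.3% | 0.2% |
| 0.5 | 0.5333 | 0.15 | 0.9% | 0.5% |

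Fall in SE = 1 - sqrt(1 - fall in variance). For example, 1 - sqrt(1 - 0.0838) = 4.3%. The last entry is 0.47% before rounding.

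Two things would raise these figures. With fewer than 15 respondents per resident, the within-resident share of the variance is larger. If EQ-5D also explained the same share of between-resident variance, the fall would be 1 - sqrt(1 - R2) at any ICC, that is 2.5% for R2 = 0.05 and 7.8% for R2 = 0.15.

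**Imbalance.** Shift in outcome SDs = EQ-5D imbalance in SDs x correlation given the other covariates. Both factors are assumed.

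- 0.2 x 0.1 = 0.02 SD
- 0.2 x 0.5 = 0.10 SD

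For comparison, the SE of the arm difference is sqrt(2 x 0.1133/87) = 0.051 SD at ICC 0.05 and sqrt(2 x 0.5333/87) = 0.111 SD at ICC 0.5. The shift is therefore 0.4 to 2.0 standard errors at ICC 0.05 and 0.2 to 0.9 at ICC 0.5. The R2 range in the table corresponds to correlations of about 0.22 to 0.39, for which the shift is 0.04 to 0.08 SD.

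**The case against.** The strongest objection is timing. Section 2.2.6 places the discussion on admission, and the only patient interview described in 2.2.5 comes after it. If EQ-5D is completed in that interview, adjusting for it would condition on something the intervention may have changed, and fear and disturbance caused by the discussion are themselves outcomes. This stands as a condition on the fix. It does not defeat the point, because the plan itself calls EQ-5D baseline data and the adjustment can be limited to values recorded beforehand.

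Second, a plan need not adjust for every variable it records. Three covariates plus resident and centre is a legitimate choice, and EQ-5D is not a baseline value of decisional conflict, knowledge, involvement or satisfaction. This also stands, and it is why the point is minor.

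Third, safeguards exist: the database and bed-manager cross-checks, eligibility checks by the study team, withholding of the intervention details and main endpoint from patients and physicians, exclusion of futile patients by GO-FAR and frailty category, and main diagnosis as a covariate. They reduce the exposure. They act on identification, eligibility and part of case mix, and not on consent to questionnaires. EQ-5D adjustment does not remove selective consent either.

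A reader might infer that residents choose patients knowing their arm, or that an unblinded person screens them. The documents do not support either: physicians are meant to be blinded, and the text does not say that the coordinator makes the eligibility check. What is established is only that patients enter after their resident has been randomised.

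**Conclusion.** The point holds as a minor one about the patient-reported secondary outcomes. EQ-5D is recorded at baseline, the adjustment set excludes it, and the order of randomisation, identification and consent leaves room for some imbalance in health status.

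The likely precision gain is small: about 1-4% of the SE at ICC 0.05 and under 0.5% at ICC 0.5, if EQ-5D explains 5-15% of within-resident variance beyond the present covariates. Protection against imbalance is the better reason, with a shift of 0.02-0.10 SD for an assumed 0.2 SD imbalance and correlations of 0.1-0.5. All of these inputs are assumptions.

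Two stronger readings should be resisted. One is that the outcomes definitely lose precision or are biased; the documents give neither the correlation nor any evidence of imbalance. The other is that the primary analysis or the sample size is wrong; the sample size reproduces and does not involve EQ-5D.

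**What to change.** - **Section 2.2.5:** state whether EQ-5D is completed before the code status discussion.
- **Section 2.3.9, if it is:** add the baseline EQ-5D score, naming which score, as a prespecified covariate in the models for decisional conflict and the other patient questionnaire outcomes. Use only values recorded before the discussion.
- **If EQ-5D is taken in the interview after the discussion:** do not adjust for it, and keep the present covariates.
- **Missing EQ-5D:** keep these patients in the models, for example by simple imputation of the baseline value without using arm or outcome.
- **Primary model:** leave unchanged, so that no patient is lost from the code status analysis for want of a questionnaire.

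The cost is a sentence in each section and a rule for missing values. No new data are needed if EQ-5D is already taken before the discussion. The report should say that this adjustment does not deal with selective consent or unmeasured differences between arms.
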